### 1.1 Need for a study

Although family caregivers have a very high share in the care of vulnerable persons and therefore the protection of this group is also very important, there are no recommendations for testing this group of persons so far. It is also unclear how high the proportion of people with a previous infection currently is, how many people have already been vaccinated and what the general attitude towards vaccination is in this population group.

The collection of these data is necessary in order to develop effective surveillance concepts for this population group, which in turn increase the protection and safety of the group of people to be cared for.

### 1.2 Objectives

The **primary objective** of the study is to determine the practicability and acceptance of different test frequencies of a simple, self-performable and self-evaluable test system (saliva test) in the previously underrepresented population group of family caregivers.

Important **secondary objectives** are:

1. obtaining data for modelling test frequency, socio-demographic data for improving mathematical models and for developing realistic surveillance systems.
2. to test the test performance (sensitivity and specificity) of self-testing systems.
3. to investigate the influence of external contacts of the carers (e.g. occupational) and the current incidence of infection and the associated potential risks of transmission of SARS-CoV-2 to the carer.
4. measure vaccination acceptance and willingness to vaccinate in this group of people.

## 2 Methods

### 2.1 Design pilot study

Prospective, longitudinal cohort study with serial self-testing with a saliva test (self-performable rapid antigen test from saliva samples) as a pilot phase over a period of 6 weeks on 45 persons. The following frequencies of self-testing will be investigated:

Group 1: 1 time per week

Group 2: 2 times per week

Group 3: every 2 days

Fifteen people are randomly assigned to each group. The allocation will be made via lots in prefabricated envelopes, which will be opened during the first visit.

The pilot phase with 45 people is to start in March 2021 (planned study period 15.03.2021 to 30.04.2021).

At the first contact (visit 1), the study design will be explained in detail to the test persons in a personal interview. They will also be informed about the blood collection and the taking of a nasopharyngeal swab for PCR testing.

After the subjects have given their written consent, the study doctor will take a blood sample to detect the presence of antibodies against SARS-CoV-2 as an indication of a previous infection and a combined throat and nasal swab to determine the SARS-CoV-2 carrier status (infection). The results will be communicated to the test persons promptly by telephone and in writing.

During this visit, the volunteers will be instructed on how to perform the saliva test, which they will carry out once on their own on site. Subsequently, the evaluation of the test is explained to the test persons. In addition, they are instructed on how to perform the saliva collection with the Salivette® system. They also carry out this test once independently on site.

In addition to the respective tests, the subjects will be given two questionnaires (questionnaire "First contact" and "Vaccinations"), which they are to complete together with the study staff at the study centre.

At the end of the first interview, each subject will be given the following materials and documents:

- corresponding number of saliva tests (depending on the randomisation group)
- appropriate number of salivettes
- written instructions for the saliva test
- form for documenting the test results (forms for documenting self-test results, Appendix 7.4.)
- stamped envelopes for the return of the salivettes
- a copy of the consent form for participation (Appendix 7.2)
- Information sheet on participation in the study (participant information, Appendix 7.1)

In the following weeks, the test persons should carry out the quick test alone at home and enter the test result in a documentation sheet. In addition, the volunteers are asked to take photos of the test cartridges with their mobile phones if possible and to bring the photos to the final interview. Furthermore, the study participants should collect saliva with the salivette system after performing the saliva test and send the sample tube to the study centre by post.

The test persons are contacted once a week by telephone by the study centre (individual interviews) in order to record possible changes from the initial interview (questions on personal contacts, questions on changes in the professional and private environment, etc.) and current surveys on the acceptance and practicability of the rapid tests and salivette systems on a weekly basis with the help of a structured questionnaire (questionnaire "Follow up"). At the same time, the result of the rapid tests is requested and an appointment is made for the next telephone survey.

At the end of the examination interval, a personal final interview takes place in the study centre, in which data on acceptance and practicability as well as suggestions for improvement on the part of the test subjects are collected again with the help of a structured questionnaire ("final interview" questionnaire). A second blood sample will be taken for a new antibody test in order to record recent infections.

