In addition, new SARS-CoV-2 variants are also spreading in Germany, for which the effects cannot yet be assessed. Since mid-December 2020, the United Kingdom (UK) has been reporting the increasing spread of the SARS-CoV-2 lineage B.1.1.7 (VOC 202012/01; VOC: variant of concern), which is characterised by an unusually high number of mutations, particularly in the viral spike (S) protein, with the help of which the virus attaches to human cells. It is now assumed that this variant exhibits increased transmissibility, resulting in a higher number of replications (2).

Herd immunity to protect against COVID-19 can be achieved either through a high vaccination rate or through natural infection. Herd immunity through natural infection would require a large population group (more than half) to undergo the disease and produce antibodies. However, it is not yet clear whether everyone acquires full immunity after passing through infection and how long this lasts. This scenario would be associated with a high number of seriously ill patients and deaths and would not be ethically justifiable (4).

The only currently viable way to achieve sufficient herd immunity is vaccination. Currently, 3 vaccines are licensed in Germany. However, due to the high demand, these cannot yet be provided in sufficient quantities. According to the RKI, only 1.5% of the adult population in Saxony-Anhalt is currently fully immunised (2 vaccinations) (5). To make matters worse, according to the recommendation of the STIKO (Standing Committee on Vaccination at the Robert Koch Institute), the vector-based COVID-19 vaccine from AstraZeneca is currently only recommended for people aged 18 to 64 years, based on the data currently available. For these reasons, the RKI has defined priority risk groups to be vaccinated who have a particularly high vulnerability or exposure risk (level 1=highest priority). Since most family caregivers are most likely to be assigned to level 3 or a higher level in the STIKO's prioritisation list, they will only benefit from this protective measure with a time lag (6).

Important measures to contain the pandemic are adherence to the AHA-L rules (distance-handwashing-everyday-mask-ventilation), quarantine measures in case of infection or contact

SuRIP/B-FAST  
Study Protocol Version 1.0,  
15.02.2021

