## **Serological and molecular biological tests**

The LIAISON SARS-CoV-2 TrimericS IgG assay (DiaSorin) is used to determine antibodies against SARS-CoV-2. If the antibody result is positive, a test with the "ImmuSAFETM Covid+" system (Aicone) is carried out to distinguish antibodies against endemic coronaviruses.

The determination of SARS-CoV-2-RNA is carried out using commercial test systems in the diagnostic area of the Institute of Medical Microbiology and Hospital Hygiene.

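### A positive spike-IgG result at Visit 8 is read as recent infection, with no stated rule, and no listed vaccination record after Visit 1, to separate vaccine responses

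*Protocol*

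**What the plan says.** **How the antibody tests are read.** Section 2.1 uses the Visit 1 sample to "detect the presence of antibodies against SARS-CoV-2 as an indication of a previous infection". For the closing visit it says "A second blood sample will be taken for a new antibody test in order to record recent infections".

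**The assay.** Under the laboratory tests in section 2.10, "The LIAISON SARS-CoV-2 TrimericS IgG assay (DiaSorin) is used to determine antibodies against SARS-CoV-2". A positive result triggers a second test, which "is carried out to distinguish antibodies against endemic coronaviruses". No other purpose is given for that second test.

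**Who is eligible.** Section 2.4 excludes only active COVID-19. Neither section 2.3 nor 2.4 mentions vaccination.

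**Vaccination in this population.** The Introduction says "Currently, 3 vaccines are licensed in Germany" and puts full immunisation (two doses) in Saxony-Anhalt at 1.5% of adults. It expects most carers to sit at priority level 3 or higher, so that "they will only benefit from this protective measure with a time lag". Section 1.1 treats the share already infected and the number already vaccinated as two separate unknowns.

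**When vaccination is recorded.** The Summary and sections 2.1 and 2.9 place the vaccination questionnaire at Visit 1. The weekly calls are described as covering contacts, changes at work and at home, and acceptance of the tests. The final questionnaire covers acceptance, practicability and suggestions.

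**Use of the data.** Section 2.9 links survey and test results through the participant ID. Section 3.1 plans descriptive frequencies of infection by sociodemographic characteristics and contact frequency.

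**The concern.** Section 1.1 sets out to learn prior infection and vaccination separately, but a spike-IgG result on its own merges them. That the licensed vaccines raise antibodies to spike is general knowledge; the protocol does not state it. Given that, a carer who is IgG-negative at Visit 1, is vaccinated in the following weeks and is IgG-positive at Visit 8 meets the protocol's stated reading of a recent infection.

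With 45 carers and six weeks, very few true infections are expected, so one or two misread results can change what section 3.1 reports. The split by contact frequency, which bears on secondary objective 3, would then partly describe who was vaccinated.

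The sharper problem is data capture. A classification rule can be written later, in an analysis plan or at the analysis stage. A vaccine dose received between Visits 1 and 8 cannot be recovered by a rule if nobody asked about it.

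**Working it through.** The protocol states no figure for expected infections or vaccinations, so there is nothing to reproduce. The following only gauges scale.

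**Inputs**
- n = 45 carers, six weeks (section 2.1).
- Weekly infection incidence i: 50 per 100,000, the only incidence in the protocol, where it is a testing threshold (Introduction); and 200 per 100,000, an assumption.
- Share newly vaccinated between Visits 1 and 8, v: 1% to 20%, an assumption. The protocol gives no figure.
- Every newly vaccinated carer is IgG-positive by Visit 8, an assumption.
- Full immunisation at baseline: 1.5%, the regional adult figure in the Introduction. The partly vaccinated share is not given.

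**Step 1: true infections.** Six-week risk p = 1 − (1 − i)^6.
- i = 50/100,000: p = 1 − 0.9995^6 = 0.0030; 45 × p = 0.13.
- i = 200/100,000: p = 1 − 0.998^6 = 0.0119; 45 × p = 0.54.

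**Step 2: vaccine seroconversions.** Expected number = 45 × v. Their share of all new positives = v / [v + p(1 − v)].

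| v | 45 × v | Share at 50/100,000 | Share at 200/100,000 |
|---|---|---|---|
| 1% | 0.45 | 77% | 46% |
| 5% | 2.25 | 95% | 82% |
| 10% | 4.5 | 97% | 90% |
| 20% | 9 | 99% | 95% |

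**Step 3: break-even.** The two sources are equal when v = p(1 − v), that is v = p/(1 + p).
- At 50/100,000: 0.0030/1.0030 = 0.3%, or 0.13 of 45 carers.
- At 200/100,000: 0.0119/1.0119 = 1.2%, or 0.53 of 45 carers.

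Both are below one carer. If only some vaccinated carers seroconvert by Visit 8, the vaccine counts shrink in proportion.

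**Step 4: baseline.** 45 × 0.015 = 0.68 fully immunised carers expected at Visit 1; the chance of at least one is 1 − 0.985^45 = 49%. These carers can be set apart through the Visit 1 vaccination questionnaire and the ID linkage in section 2.9, provided the questionnaire records doses, as section 1.1 implies.

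**The case against.** **The weekly calls may already ask.** Section 2.1 gives them the purpose of picking up anything that has changed since the first interview, and its list of topics is explicitly open-ended. A new vaccination is such a change, because the vaccination questionnaire belongs to Visit 1. The follow-up and final forms are not shown. This stands: a reader might infer that vaccination is asked only once, but the protocol shows only that no later item is listed.

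**Nothing says vaccine responses will be counted as infections.** Section 3.1 does not define infection by serology. Section 2.7 treats infection as confirmed by PCR, saliva samples are also sent in for PCR, and section 2.1 calls antibodies only an indication of past infection. An analysis plan could add a rule. This stands against the claim that such results will be miscounted. It does not remove the stated purpose of the Visit 8 sample, and no rule can use doses that were not recorded.

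**Uptake may be slow.** The Introduction expects a delay for most carers, so it does not support the picture of a group being vaccinated throughout the study. The 5% to 20% rows have no basis in the documents. At 1% and 200/100,000 the vaccine share is 46%, which is not dominance. Doses given shortly before Visit 8 may not yet show. All of this limits the size of the problem, not its existence.

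**Stronger readings that the documents do not support.** A reader might infer that baseline seroprevalence is also swamped; about 0.7 carers at the stated 1.5%, separable by linked data, does not show that. A reader might infer that the modelling data are corrupted; objective 1 in section 1.2 names test frequency and sociodemographic data and does not mention serology. A link between misclassification and occupation through vaccination priority is possible but not shown. Whether the second antibody test could separate vaccination from infection is not stated either way.

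**Conclusion.** The point holds in a limited form. The protocol reads spike IgG as infection, admits vaccinated carers, states no means of separating the two sources of antibody, and lists no vaccination record after Visit 1. Vaccine seroconversions between Visits 1 and 8 can therefore be misread as recent infections.

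On the assumptions above, they would make up between 46% and 99% of new positives. The result depends on assumed uptake, full seroconversion among the vaccinated and, at the upper end, an assumed incidence of 200 per 100,000. The break-even calculation is less dependent on the choice of uptake: at either incidence, less than one additional seroconverting vaccinee is enough to equal the expected true infections.

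The effect is confined to descriptive, secondary results. The primary objective, practicability and acceptance of test frequencies, is untouched. This should be fixed, but it is not a condition for the study to proceed.

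**What to change.** 1. **Data capture.** Add one item, vaccine dose and date since the last contact, to the weekly follow-up questionnaire and to the Visit 8 questionnaire. If the forms already contain it, say so in section 2.1. Confirm that the Visit 1 vaccination questionnaire records doses and dates as well as attitudes.
2. **Definitions in sections 2.1 and 3.1.** Serological recent infection: IgG-negative at Visit 1 and IgG-positive at Visit 8, with no vaccine dose before Visit 8. Serological previous infection: IgG-positive at Visit 1 with no prior dose.
3. **Reporting.** Show vaccinated participants separately, as not classifiable by spike IgG, and give the denominator for each serological frequency.

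The cost is one questionnaire item, one classification rule and a smaller denominator for serology: at 1% to 20% uptake, 0.45 to 9 of the 45 carers would leave it, in addition to those vaccinated before Visit 1. Keeping vaccinated carers in the denominator would require a non-spike antibody result, and the protocol does not say whether the second test supplies one.

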## Recruitment of participants

The subjects are recruited by advertisement in the local print media. Interested persons should contact the study secretariat by telephone.

## Follow-up recruitment

If subjects leave the study during the first week, a follow-up recruitment will take place. For this purpose, interested persons who responded to the advertisement but could not be included in the initial recruitment will be contacted by telephone.

## 2.2 Schedule

### Milestones:

|                   |                             |                        |                        |
|-------------------|-----------------------------|------------------------|------------------------|
| 19.02.2021        | 15.03.2021                  | 15.06.2021             | 01.08.2021             |
| Ethics submission | Start pilot phase (6 weeks) | End of data collection | End of data evaluation |

### Pilot study

|                    | Jan | Feb | Mar | Apr | May | Jun | Jul | Aug | Sep |
|--------------------|-----|-----|-----|-----|-----|-----|-----|-----|-----|
| Preparation        |     |     |     |     |     |     |     |     |     |
| Recruitment        |     |     |     |     |     |     |     |     |     |
| Study inclusion    |     |     |     |     |     |     |     |     |     |
| Study period       |     |     |     |     |     |     |     |     |     |
| Study finalisation |     |     |     |     |     |     |     |     |     |

### **2.3 Inclusion criteria**

- Minimum age of 18 years
- Family carers with at least 2 contacts per week of at least 30 minutes duration with the person to be cared for.
- Caring relatives have external contacts (e.g. occupation)
- Written informed consent to participate in the study.
- Written consent for blood sampling (2x) and for taking a nasopharyngeal swab (1x).

### **2.4 Exclusion criteria**

- active COVID-19 disease

### **2.5 Procedure in case of withdrawal of consent**

If a subject withdraws his/her consent to participate in the study, this must be done in writing. The subject will then receive written confirmation of receipt. The data collected up to that point will be analysed.

### **2.6 Procedure in case of occurrence of COVID-19 infection during the study**

The test persons are informed that if symptoms of a cold appear, they must immediately take measures to distance themselves and contact their family doctor. The general practitioner decides on the clarification of an acute COVID-19 disease. Alternatively, the test persons will be referred to the fever outpatient department of the university hospital for testing by means of PCR. The volunteers are informed that the self-test does not replace these measures.

If a COVID-19 infection is detected, the volunteers must inform the study centre. They will then be excluded from the study.

### **2.7 Procedure in case of positive saliva test**

If the saliva test is positive, the subject must immediately contact the study centre by telephone.

To exclude a COVID-19 infection, a combined throat and nose swab will be performed by trained staff at the study centre or at the fever outpatient clinic at Magdeburg University Hospital and a PCR test for SARS-CoV-2 will be performed.

If the PCR result is negative, an infection is excluded at the time of sample collection. The test person will receive a self-monitoring form to be completed daily and will initially remain in the study. If symptoms of a COVID-19 infection occur, the study centre must be informed and the family doctor contacted (see point 2.6).

If the PCR result is positive, a SARS-CoV-2 infection is confirmed. The subject must then go into home isolation. The result of the PCR test is communicated to the public health department, which will arrange for further measures.

### **2.8 Procedure in the event of the death of the person being cared for**

If the person being cared for dies during the course of the study, the participant no longer belongs to the group of people being studied and is excluded from the study. The test person may keep the saliva tests that have been handed out and not yet used up to this point.

## 2.9 Data collection and data flow

### Data collection:

There will be 2 visits with personal presentation at the study centre. The other contacts are made by telephone in the form of individual interviews.

### Visit schedule:

|                                                        | Visit 1
Inclusion | Visit 2
Week 1 | Visit 3
Week 2 | Visit 4
Week 3 | Visit 5
Week 4 | Visit 6
Week 5 | Visit 7
Week 6 | Visit 8
Closing |
|--------------------------------------------------------|----------------------|-------------------|-------------------|-------------------|-------------------|-------------------|-------------------|--------------------|
| Personal visit                                         | X                    |                   |                   |                   |                   |                   |                   | X                  |
| Antibody determination
Blood sample 10ml
serum   | X                    |                   |                   |                   |                   |                   |                   | X                  |
| PCR test/
nasopharyngeal swab                       | X                    |                   |                   |                   |                   |                   |                   |                    |
| Questionnaire                                          | X                    |                   |                   |                   |                   |                   |                   | X                  |
| Randomisation                                          | X                    |                   |                   |                   |                   |                   |                   |                    |
| Self-test by participants
(saliva test, salivettes) | X                    | X                 | X                 | X                 | X                 | X                 | X                 |                    |
| Query test result (by
telephone)                    |                      | X                 | X                 | X                 | X                 | X                 | X                 |                    |
| Questionnaire
(by telephone)                        |                      | X                 | X                 | X                 | X                 | X                 | X                 |                    |

The initial survey, vaccination acceptance and willingness to be vaccinated are recorded pseudonymously with paper questionnaires during the initial interview at the study centre and are kept by the IMMB during the pilot phase and forwarded to the Institute for Social Medicine and Health System Research (ISMG) of the University Medical Centre Magdeburg for later evaluation. The telephone survey of the follow-up questionnaires is conducted by IMMB staff and is also passed on to the ISMG in pseudonymised form after completion of the pilot study.

